### Unscheduled pregnancy

Any pregnancies which occur during study period should be reported to corresponding investigator, and all study related-treatment should be stopped consequently. Investigator should report to both CRO and SPONSOR using specific-pregnancy form. The pregnant patient should be followed-up till delivery, the outcome of pregnancy and delivery should be reported to both CRO and SPONSOR. The pregnancy occurs with participant’s wife also should be reported and followed.

### Recording and reporting of SAE

The investigator is responsible for the detection and documentation of events meeting the criteria and definition of a serious adverse event (SAE) as provided in this protocol. Each patient will be instructed to contact the investigator immediately should the subject manifest any signs or symptoms they perceive as serious.

SAEs will be reported concurrently to CRO, SPONSOR, Principle Investigator, IRB, and SFDA within 24 hours, once the investigator determines that the event meets the protocol definition of a SAE. The SAE Form will always be completed as thoroughly as possible with all available details of the event, signed by the investigator (or designee), and will always provide an assessment of causality at the time of the initial report.

After the initial SAE report, the investigator is required toactively follow each subject and provide further information to the CRO, SPONSOR, Principle Investigator, IRB, and SFDA on the subject’s condition. Investigators will follow-up subjects with SAEs until the event has: resolved or subsided or stabilized or disappeared or the event is otherwise explained, or the subject is lost to follow-up.

### Important noticeable event

Important noticeable events is defined as any event which must be solved and recorded, such as treatment stopping, dose reducing, concomitant medication and withdrawal.

### Procedure for causal relationship assessment

The confirmation of SAE and its causal relationship with the vaccines will be conducted by corresponding investigator and clinical monitor, and then reported to Principle investigator, CRO and SPONSOR. If the agreement for a certain SAE cannot be reached among investigator, CRO and SPONSOR, Adverse Event Evaluation Committee authorized by the Ministry of Health will therefore be invited for confirmation.

## Efficacy measurement

The efficacy measurement will rely on the following laboratory testing:

- 1. HBV DNA
  2. HBeAg
  3. HBeAb

### Definition of endpoints

The virologic response will be assessed four weeks after the end of treatment (week 24) and at the end of follow-up (week 44). HBeAg seroconversion was defined by the loss of HBeAg and the presence of anti-HBe antibody. Suppression of HBV DNA was defined as > 2 log10 decrease of viral load.

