| Safety endpoints | Adverse events, laboratory testing, systemic and local reactions. |
| Study procedure | - After the protocol being approved by the ethic committee, and inform consenting, patients will be screened and assigned to 30 μg, 60 μg YIC and placebo groups randomly; - Study agents will be given at baseline (0 week), 4th, 8th, 12th, 16th and 20th week; - Treatment will be ended at 20th week, and followed both at 24th week and by 44th -week for efficacy follow-up; - Subjects will be interviewed at baseline, 4th, 8th, 12th, 16th, 20th, 24th, 36th, and 44th week. Each interview will include blood cell count and biochemical liver function testing. Virologic and HBeAg/anti-HBe from samples of all patients will be assayed at the same time for serum at baseline, 12th, 24th, 36th, and 44th week at the reference lab after 44-week follow-up. - Adverse events, and concomitant medication will be recorded at each interview. |

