### Reference lab

In order to ensure a standardized and qualified clinical assay, the clinical laboratory of Beijing Ditan Hospital will be assigned as the reference lab for this study. Serum samples collected during the study period should be transported to reference lab for repeating / testing by airway at the end of study.

Hepatitis B virus markers (HBsAg, HBeAg and HBeAb) and virus load (HBV DNA) will be tested at the reference lab. Hepatitis B virus makers will be assayed by Abbott reagent (Abbott Axisim), and the virus load will be determined by real-time PCR **(**PiJi, Shenzhen Co, China with a detection limit of 500 copies/mL**).**

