### Primary endpoint

The primary endpoint was defined as loss of HBeAg, or presence of anti-HBe antibody or suppression of HBV DNA.

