### Secondary endpoint

The secondary endpoint was designated as both HBeAg seroconversion and suppression of HBV DNA.

- 1. Basic treatment

Considering the ethical issue, each patient who participates in this trial will be given basic treatment besides of study agents throughout 44-week study period as following:

- 1. Silymarin, 50 mg/tablets, 3 tablets per time, tid；
  2. Hu Gan Tablet, 0.36g per tablet, 4 tablets per time, tid.
  3. Concomitant medication

Concomitant medication is defined as: any vaccine, any other medication relevant to the protocol and administrated during the period starting from prior to treatment until the end of follow-up.

At each study center, the investigator should question the patient about any medication taken between two injections. All concomitant medication must be recorded in the CRFs with the trade name, generic name, indication, dose, route of administration, start and end dates of treatment.

The flowing drugs, treatments and behaviours are not allowed:

- 1. Any immunosuppressive or immunostimulant therapy, anti-viral therapy, drugs that have effects on decreasing the level of ALT, androgenic drugs, steroids, contraceptive drugs;
  2. Any investigational or non-registered anti-HBV drug, herbs or other patient self-chozen therapies
  3. Usage of acetaminophen more than 4 g per day;
  4. Intake of spirits more than 20 g per day;

1. Data management

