# Statistical Methods

All data will be double entered into custom-made data entry programs. The data management programs include range and consistency checks. An SAS program (SAS Institute Inc., Cary, NC, USA ) will be applied for statistical analysis.

- 1. Safety

The safety analysis will be performed based on the safety set (SS). It will include patients who received at least one injection, and completed at least one interview of safety evaluation after injection.

Three-wise comparison employed the chi square test, or Fisher’s exact test when data were sparse, for dichotomous outcomes will be performed to test the difference of occurrence of adverse events among placebo, 30 μg YIC and 60 μg YIC groups. A p-value < 0.05 (two-tailed) will be considered statistically significant.

- 1. Efficacy

The efficacy analysis will be conducted based on both full analysis and per-protocol sets. For full analysis set (FAS), it will include patients who were randomized, received at least one injection, and completed at least one interview of efficacy evaluation after injection. The intent-to-treat principle will be applied for the dataset. For per protocol set (PPS), it will include patients who met following three conditions：

1. Baseline information are available；
2. Complete full course of treatment and follow-up without protocol violation；
3. With good compliance (between 80% and 120%）.

For those important indicators, the missing data will be estimated using the most previous observation (LOCF, last observation carry forwards).

The primary efficacy hypotheses will be tested for response rate of primary endpoint in 30 μg YIC or/and 60 μg YIC groups > that in placebo group (2-tailed). The Chi square test, or Fisher’s exact test when data were sparse, will be employed. A p-value, point estimate, as well as confidence interval will be calculated.

The secondary efficacy outcomes will be summarized in a similar fashion.

Repeated measures analysis will be performed using a generalized estimating equations (GEEs) method to adjust the dependence among repeated observations made on the same patient while testing the group and time effects. A p-value < 0.05 (two-tailed) will be considered statistically significant.

- 1. Sample size

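### HBV DNA is quantified at five time points, but both named efficacy endpoints use it only as a yes/no fall of more than 2 log10, with no covariate adjustment for baseline values

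*Protocol*

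**What the plan says.** On measurement, section 4.4.1 states that "the virus load will be determined by real-time PCR", "with a detection limit of 500 copies/mL", at a single reference laboratory. The synopsis says that the virologic and HBeAg/anti-HBe samples "will be assayed at the same time for serum at baseline, 12th, 24th, 36th, and 44th week at the reference lab", once the 44-week follow-up is over.

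On endpoints, section 4.6.1 sets weeks 24 and 44 as the assessment times and fixes the cut: "Suppression of HBV DNA was defined as > 2 log10 decrease of viral load". Section 4.6.2 builds the primary endpoint on it: "The primary endpoint was defined as loss of HBeAg, or presence of anti-HBe antibody or suppression of HBV DNA". Section 4.6.3 uses the same cut: "The secondary endpoint was designated as both HBeAg seroconversion and suppression of HBV DNA".

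On analysis, section 6.2 tests the primary endpoint by chi-square, or by Fisher when data are sparse, with no covariates. It adds that "The secondary efficacy outcomes will be summarized in a similar fashion". It also plans a GEE repeated-measures analysis of group and time effects, but does not say which variable is modelled or whether a baseline term enters.

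On dose, optimising dosage is an objective (section 3). Section 2.2 says the dose is to be worked out by comparison with placebo, and the hypotheses in 6.2 and the sample size in 6.3 are each dose against placebo.

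**The concern.** Viral load is a continuous quantity here, yet each endpoint keeps only whether a patient crossed one line. The single secondary endpoint is a rarer yes/no subset of the primary, so it adds no graded information. Baseline log10 HBV DNA and ALT, collected in every patient at screening, are not used as covariates.

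What is at stake is modest. If both doses beat placebo, or neither does, the reader will want to know how far the antiviral effects of 30 µg and 60 µg differ. On the endpoints as defined, that can be described only by the difference between two proportions, which will be imprecise at this sample size. No predefined estimate on the log10 scale would stand beside it.

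**Working it through.** **Inputs.** Section 6.3 gives response rates of 35% (60 µg), 20% (30 µg) and 3% (placebo), 78 per arm, alpha 0.05, power 80% and dropout 20%. Completers per arm are 78 × 0.8 = 62.4, taken as 62. Tests are two-sided at 0.05. The protocol gives no SD of log10 change, no correlation with baseline and no response rate for DNA alone, so those are assumptions below.

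**The plan's own figure.** The binding comparison is 20% vs 3%. Fisher's exact test at 62 completers has 81.9% power, which is consistent with 78 per arm. The unpooled two-proportion formula at alpha 0.025 also gives it: 62.2 / 0.8 = 77.7. The protocol does not say which was used.

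**Yes/no endpoint (exact enumeration).**

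| Comparison | Test | 62 per arm | 78 per arm |
|---|---|---|---|
| 20% vs 3% | chi-square | 89% | 95% |
| 20% vs 3% | Fisher | 82% | 92% |
| 35% vs 20% | chi-square | 47% | 56% |
| 35% vs 20% | Fisher | 39% | 50% |

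For 35% vs 3%, power exceeds 99%. For 35% vs 20%, the pooled formula needs 138 completers per arm for 80% power.

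**Log10 scale for 60 vs 30 µg, under three assumptions.**

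1. *Every response is a DNA response, from a common-SD normal shift across the cut.* The shift is d = z(0.35) − z(0.20) = −0.385 + 0.842 = 0.456 SD. The noncentrality is d√(n/2) = 0.456 × √31 = 2.54, which gives about 71% power at 62 per arm and 81% at 78. The number needed for 80% is 76 per arm, so the cut costs 1 − 76/138 = 45% in sample-size terms.
2. *Half of each effect over placebo is on DNA.* The DNA rates become 3 + 32/2 = 19% and 3 + 17/2 = 11.5%. Then d = −0.878 + 1.200 = 0.322 SD. Unadjusted power is 43% at 62 per arm and 52% at 78. With an assumed correlation r = 0.5 between change and baseline, d is divided by √(1 − 0.25) = 0.866, and power at 62 is 54%. The comparator is chi-square on the composite: 47% at 62 and 56% at 78.
3. *All-or-none response: 35% vs 20% have a large fall, the rest about 0.3 log10.* In simulation (3,000 runs per cell, within-group SD 0.5 to 1.0 log10, responders falling 2.8 to 4.3 log10), the t-test has 30–43% power and chi-square 31–46%. A baseline-adjusted analysis with a floor at 500 copies/mL has 40% against 46% for the cut; for 20% vs 3% it has 72% against 87%. That run assumed responders fall about 3.5 log10, and baseline mean 7.5, SD 1.2, truncated at 5.

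**Baseline adjustment of the responder test.** In simulation of a likelihood-ratio logistic test at 62 per arm, a baseline score with an assumed odds ratio of 2 to 3 per SD raises power for 35% vs 20% from about 47% to 51–56%. Allowing for simulation error, the gain is roughly 2 to 9 points.

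**Floor.** 500 copies/mL is 2.70 log10. A patient entering at 10⁵ copies/mL can show a fall of at most 5.00 − 2.70 = 2.30 log10, so a log10 analysis must allow for censoring.

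**The case against.** The best case against the point has four parts.

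*Supportive continuous analyses and covariates belong in a SAP.* This stands in part, since only the protocol is at hand. But the protocol itself states the full endpoint list and names an unadjusted test, so improving those is a comment on what it fixes.

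*The GEE may already model log10 HBV DNA.* It may. The outcome is unnamed, so it cannot be said that the quantitative data go unused. What can be said is that no quantitative measure is defined.

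*Dose is judged against placebo, and those comparisons are adequately powered.* This stands. The 47% concerns a 60 vs 30 µg contrast that the protocol does not list as a hypothesis. It shows how imprecisely the doses can be compared and does not mean that a planned test fails.

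*The log10 scale may gain nothing.* This stands. The 35% and 20% are rates for a composite that includes HBeAg loss and anti-HBe, so reading them wholly as a DNA shift is the favourable case. Phase IIa, with DNA suppression in 4 of 36 patients, is too sparse to tell a shift from an all-or-none pattern.

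A reader might go further and infer that most of the viral-load information is discarded. On the protocol's rates the loss is about 45% under the pure shift, and there is none under all-or-none response. Nor is the loss of information greatest between the doses. Under a shift the cut retains φ(z)²/[p(1−p)] of the information: 49% at a 20% rate and 60% at 35%, but only 16% at the 3% placebo rate, where power is adequate anyway. A 1.9 log10 fall is not always scored as no response, because HBeAg loss or anti-HBe alone meets the primary endpoint. Baseline is not ignored either: the fall is measured from it, and only covariate adjustment is absent.

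**Conclusion.** The point holds in a limited form. HBV DNA is quantified five times, both named endpoints reduce it to one cut, the stated test has no baseline covariates, and no quantitative viral-load outcome is named. The placebo comparisons are sound as binary tests (82–89% for 20% vs 3% at 62 per arm).

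The possible cost is precision in describing 60 vs 30 µg, where the yes/no test has 47% power (Fisher 39%). Whether the log10 scale improves on that depends on assumptions the protocol does not supply: about 71% under a pure normal shift, 43% unadjusted (54% at r = 0.5) with half the effect on DNA, and no gain or a loss under all-or-none response. The gain from baseline adjustment of the responder test rests on an assumed odds ratio.

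These results support adding a log10 measure alongside the responder endpoint. They do not support replacing it, or any claim that the primary analysis is inadequate.

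**What to change.** Keep the responder endpoint as primary and the sample size as it is.

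1. In 6.2, analyse the responder endpoint with a logistic model containing arm, baseline log10 HBV DNA and baseline ALT, and report a standardised risk difference with its 95% CI. Keep chi-square/Fisher as the unadjusted check. Provide for Firth estimation: at 3% of 62, only about two placebo responders are expected.
2. In 4.6.3 and 6.2, name change in log10 HBV DNA from baseline at weeks 24 and 44 as a supportive secondary endpoint in the full analysis set. Adjust for baseline log10 HBV DNA and centre, and treat values below 500 copies/mL as left-censored (for example a Tobit model). Report estimates and 95% CIs for each dose vs placebo and for 60 vs 30 µg. Alternatively, name log10 HBV DNA as the GEE outcome.

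The cost is a few lines of text, one more secondary result labelled as outside the primary decision, and some modelling of censored or sparse data. No further samples, visits, assays or patients are needed. Because the reference-laboratory assays run only after week 44, the measure can be defined before any of those results exist.

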### Primary endpoint

The primary endpoint was defined as loss of HBeAg, or presence of anti-HBe antibody or suppression of HBV DNA.

### Secondary endpoint

The secondary endpoint was designated as both HBeAg seroconversion and suppression of HBV DNA.

- 1. Basic treatment

Considering the ethical issue, each patient who participates in this trial will be given basic treatment besides of study agents throughout 44-week study period as following:

- 1. Silymarin, 50 mg/tablets, 3 tablets per time, tid；
  2. Hu Gan Tablet, 0.36g per tablet, 4 tablets per time, tid.
  3. Concomitant medication

Concomitant medication is defined as: any vaccine, any other medication relevant to the protocol and administrated during the period starting from prior to treatment until the end of follow-up.

At each study center, the investigator should question the patient about any medication taken between two injections. All concomitant medication must be recorded in the CRFs with the trade name, generic name, indication, dose, route of administration, start and end dates of treatment.

The flowing drugs, treatments and behaviours are not allowed:

- 1. Any immunosuppressive or immunostimulant therapy, anti-viral therapy, drugs that have effects on decreasing the level of ALT, androgenic drugs, steroids, contraceptive drugs;
  2. Any investigational or non-registered anti-HBV drug, herbs or other patient self-chozen therapies
  3. Usage of acetaminophen more than 4 g per day;
  4. Intake of spirits more than 20 g per day;

1. Data management

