### Inclusion criteria

- 1. Patients provide written inform consent;
  2. Patients aged 18 to 65years regardless of gender;
  3. Patients with HBsAg positive in the preceding 6 months;
  4. Patients with HBeAg positive, HBeAb negative, and virus load (HBV DNA)  1105 copies/ml;
  5. Patients with abnormal ALT (between 2- and 10-fold of cutoff value). If abnormal ALT had appeared in the preceding 6 months, the interval period should be longer than one month;
  6. For reproductive age women, the uric or blood pregnancy test should be negative. Both male and female patients should not have birth plan until 3 months after the completion of study.

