### Exclusion criteria

1. Pregnancy women or lactation women;
2. Patients who have received antiviral therapy or immunosuppressive drugs, such as adrenal cortical hormone, thymic peptide 1 in the preceding 6 months or long-term;
3. Patients co-infected with HAV, HCV, HDV, HEV and HIV;
4. Patients with history of or current allergic diseases, hypersensitivity to any biological product injection, and autoimmune diseases;
5. Patients who have received hepatotoxic drugs in the preceding 6 months;
6. Patients with confirmed or suspected liver cirrhosis, or compensated cirrhosis;
7. Patients with confirmed or suspected primary hepatic carcinoma or AFP>100ng/ml;
8. Patients with other liver diseases, including chronic alcoholic hepatitis, drug-induced hepatitis, autoimmune hepatitis（antinuclear antibody > l:100）、Kinnier-Wilson syndrome, and hemachromatosis;
9. Life-threatening or serious cardiac, respiratory, gastrointestinal, renal, endocrine, hematological or immunological disorders which, in the opinion of the investigator, will be **excluided** in the study;
10. Serum creatinine > 1.5-fold of upper limit of cutoff value;
11. Blood platelets count < 75×109/L；
12. Leucocyte count < 3×109/L；
13. Haematoglobin <11.5g/dL（female） or <12.5g/dL（male）;
14. Serum total bilirubin  2-fold of upper limit of normal value;
15. Patients with history of drug addiction, including alcohol abuse (40g/day) in the preceding 6 months;
16. Patients had participated in other clinical trials in the preceding 3 months.
    1. Study procedure

The core procedures see appendix 2. The entire study duration will be 46 weeks, including 2-week run-in, 20-week treatment and 24-week follow-up.

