#### Vaccination

Study agents will be administrated to each patient according to the allocation number on the label of study agent.

Precaution

1. Products should be shaken thoroughly prior to administration;
2. Products should be inspected visually for particulate matter or discoloration prior to administration;
3. Epinephrine should be available for potential immediate allergic reactions;
4. Injection should be carried out by experienced and per-designated personnel;
5. All used study agent-related things including empty ampoules, packages and labels should be kept;
6. To ensure the accuracy of dosage, one mL syringe should be used for injection.

Study agent code will be assigned strictly to patient in terms of the recruitment sequence. All instruction on the label of study agent will be followed.

Administration

With thorough agitation, 1 mL (for either 30 g YIC group or 60 g YIC group) vaccine will be drawn from ampoule using 1 mL syringe, and will be injected to patient in the deltoid region. The injection will be given at day 1, week 4, 8, 12, 16 and 20.

With thorough agitation, 1 mL placebo will be drawn from ampoule using 1 mL syringe, and will be injected to patient in the deltoid region. The injection will be given at day 1, week 4, 8, 12, 16 and 20.

A total of 240 chronic hepatitis B patients will be recruited, and assigned to 30 g (group 2), 60 g YIC (group 3), and placebo group (group 1) in a ratio of 1:1:1.

The immediate reaction within 30 minutes after injection will be observed. Concurrently, basic medication (Silymarin and Hu Gan Tablet) will be distributed to each participated patient. To record the solicited and non-solicited reaction in the following 4 weeks after injection, diary card will be distributed. Corresponding instruction for filling in out will be given by investigator.

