### Visits during the treatment period (Week 4, 8, 12, 16, and 20 ± 4 days after the initial dose)

During the treatment period, interview and physical examination (temperature, heart rate, and blood pressure) will be conducted at week 4, 8, 12, 16, 20 and 24. Concurrently, a serials test will be performed for each recruited patients, including liver function (ALT、AST、TBil、DBil、TP、ALB、and AKP), biochemical tests, blood cell count, microscopyd, uric testsd, renal function and assays for electrolytes.

Two vials of serum sample (2 mL for each) will only be required from each patient at week 12. The serum samples will be stored at minus 70 centigrade freezer for virologic response testing at reference lab at the end of study.

The same study agent will be administrated to each patient once every four weeks till week 20. The immediate reaction within 30 minutes after injection will be observed at research centers. A diary card to record the solicited and non-solicited reaction in the following 4 weeks after each injection will be distributed to patient with the basic medication. The diary card from the pervious vaccination will be collected at the beginning of each injection.

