### Discontinuation/Withdrawal

Any patient who had signed a consent form, and meet the following criteria will be defined as premature withdrawal.

1. Patients who request to quit themselves;
2. Patients who violate the study protocol;
3. Patients who become pregnancy;
4. Patients who are unblinded due to SAE;
5. Patientsduring the treatment period who developed the following symptoms
   - - - Hepatic cirrhosis
       - Hepatic failure
       - And hepatoma.

If the withdrawal occurs due to the adverse events or abnormal laboratory tests, details should be recorded in the CRFs.

- 1. Laboratory assay

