### Testing during follow-up period

In each study center, liver function, renal function, Electrolytes, blood cell count and uric testing will be performed for all enrolled patients at week 4, 8, 12, 16, 20, 24, 36 and 44.

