### Surveillance of adverse events following injections

A surveillance system will be implemented to document the safety profile of the study agents during the study period. Surveillance of vaccine safety will be carried out following the WHO guidelines. At each study center, all adverse events either observed by the investigator or reported by the patients spontaneously will be evaluated by the investigator. Type III allergic reactions, such as fever, redness, pruritus, rash, joint pain and arthritis should be included in the AEs observation in this study.

The following surveillance methods will be applied to detect and record adverse events:

*Observation 30 minutes after vaccination*

All patients will be asked to remain at the vaccination site for 30 minutes immediately after vaccination to observe the immediate adverse events. Immediate serious adverse events will be treated following the WHO guidelines and recorded in the Serious Adverse Event Report Form by trained investigators. Each study center will be equipped with basic emergency equipment in case of an immediate SAE.

*Adverse events between two injections*

The potential AEs occurs between two visits will be recorded to the diary card by patients. At the beginning of each visit, investigators should query patients about AEs may occur during the two visits, and collect the diary card from last visit.

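### Contraceptive drugs are banned with no other method required in the eligibility or medication sections, and five of the six injections have no scheduled pregnancy test

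*Protocol*

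**What the plan says.** **Contraception.** Section 4.8 (Concomitant medication) lists treatments that patients may not take, among them "androgenic drugs, steroids, contraceptive drugs". It gives no exception, names no substitute method and states no duration for the ban. Inclusion item 6 (section 4.2.1) asks for a negative pregnancy test at entry in women of reproductive age and adds: "Both male and female patients should not have birth plan until 3 months after the completion of study". It names no method.

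**Dosing.** Section 4.3.3 sets six injections: "The injection will be given at day 1, week 4, 8, 12, 16 and 20".

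**Pregnancy testing.** The HCG test is in the screening list (section 4.3.2), with a footnote placing it 24 hours before treatment. Its row in Appendix 2 has one mark, in the screening column. For the later visits, section 4.3.4 says "a serials test will be performed for each recruited patients, including liver function", followed by other routine laboratory tests, with no HCG. Section 4.4.3 adds that "uric testing will be performed for all enrolled patients at week 4, 8, 12, 16, 20, 24, 36 and 44".

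**Intent.** Section 4.2.2 excludes "Pregnancy women or lactation women". Section 4.3.8 counts "Patients who become pregnancy" among premature withdrawals. Section 4.5.9 requires any pregnancy to be reported and study treatment to be stopped.

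**The concern.** Three provisions (exclusion, withdrawal, stopping treatment) show that the protocol means to keep pregnant women off the study agent. The test schedule does not carry that intent past the first dose. A site that follows the schedule exactly could inject a woman in an early, unrecognised pregnancy, because nothing scheduled after screening would show it.

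The medication list adds to this. It takes away one class of contraception, and the two sections where a replacement would naturally stand do not require one. Item 6 states an intention (no planned birth) rather than a method.

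What is at stake is avoidable exposure of a pregnancy to an investigational product for which this protocol gives no reproductive-toxicity data. The efficacy analysis is not at stake.

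**Working it through.** The protocol states no figure on this point, so the check is a count of scheduled injections against scheduled pregnancy tests.

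| Time | Injection (4.3.3, Appendix 2) | Scheduled HCG test (4.3.2, 4.3.4 to 4.3.6, 4.4.3, Appendix 2) |
| --- | --- | --- |
| Screening | no | yes |
| Day 1 | yes | covered by the screening test |
| Weeks 4, 8, 12, 16, 20 | yes, at each | none |
| Weeks 24, 36, 44 | no | none |

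- Injections: 1 + 5 = 6.
- Injections with a scheduled test before them: 1.
- Injections without one: 6 - 1 = 5.

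Two readings could change the count.

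1. *Does the 24-hour footnote mean before every injection?* It does not say first treatment. But it hangs on the screening list item and on an Appendix 2 row whose only mark is at screening. The column for day -14 to day -1 fits a test one day before the first dose. The single-test reading is the one the document supports.
2. *Do the later urine tests include HCG?* No. The pregnancy test has its own item in the screening list and its own row in Appendix 2, separate from the urine test.

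On contraception, sections 4.8 and 4.2.1 read together give a ban on contraceptive drugs, an instruction not to plan a birth until 3 months after completion, and no required method.

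The count does not convert into a number of exposed pregnancies. That would need the sex split, contraceptive use, pregnancy rate and time to recognition, and the protocol gives none of them.

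**The case against.** The best defence is that the protocol is consistent on an entry test and has several later safeguards. Patients attend every four weeks and are examined. Section 4.5.2 says that "investigators should query patients about AEs may occur during the two visits", and section 4.8 has them asked about medication between injections. Pregnancy leads to withdrawal and to stopping treatment, with follow-up to delivery. Item 6 addresses conception throughout the trial, for both sexes.

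This stands in part: the safeguards give a chance to hear of a pregnancy. But the physical examination is described as temperature, heart rate and blood pressure, and the rest depends on the patient already knowing. None of it would show an early pregnancy before the next injection.

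A reader might infer more than the text supports:

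- *That women are taken off contraception and left unprotected.* Only drugs are banned, so barrier and other non-drug methods remain open. The protocol does not say whether a current user must stop her drug or would simply not be enrolled. That the ban runs to the end of follow-up is only an inference from the definition of concomitant medication. The consent pages, not available here, may give contraceptive advice.
- *That a typical number of injections per affected pregnancy can be stated.* Any such figure would rest on assumed conception and recognition times.
- *That fetal harm is shown or likely.* The protocol gives no data either way.

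**Conclusion.** The point holds as a modest patient-safety improvement. Five of six injections have no scheduled pregnancy test, and contraceptive drugs are banned without a required alternative in section 4.8 or inclusion item 6. The count of 5 is the only size that the document supports. It rests on reading the footnote and Appendix 2 together as a single test at screening, which is the natural reading.

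The testing half does not depend on the consent pages. The contraception half does to some extent, and is limited to the two sections named. The number of exposed pregnancies and any harm cannot be estimated. The primary comparison is not affected.

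**What to change.** Two changes:

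1. **Appendix 2.** Mark the HCG row at weeks 4, 8, 12, 16 and 20 for women of reproductive age, use the urine already collected at those visits, and read the result before the injection. Five explicit marks also settle any doubt about the 24-hour footnote.
2. **Inclusion item 6.** Require women of reproductive age, and men with partners of reproductive age, to use an effective non-drug contraceptive method from screening until 3 months after completion. That end point is the one the item already sets.

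The ban on contraceptive drugs can stay.

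**Cost.** Five urine HCG tests per woman of reproductive age. The sex split is not given. If such women are 10% to 50% of the 240 patients (an assumption), that is 5 × 24 = 120 to 5 × 120 = 600 tests over the whole trial. Injection visits become slightly longer, and a few patients may decline because a method is required.
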